### Randomization

ALEA (a software package to support online randomization in healthcare research) will be used to randomly allocate the participant to either the intervention or control group (allocation rate 1:1). This computer-based system ensures allocation concealment. In order to create equal comparison groups and prevent allocation bias, randomization will be stratified for three different groups (that is, conclusive versus inconclusive DNA test result) and whether or not the counselee has been diagnosed with cancer. To balance group sizes, random block randomization will be used with a maximum block size of 8 and block size factor 5.

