### Participants

Consecutive counselees visiting the department of Clinical Genetics of three university hospitals in the Netherlands will be recruited. The sample comprises the following groups of counselees: those with conclusive test results (a pathogenic mutation has been found), those with an inconclusive test result, and those in whom DNA testing is not possible. For the latter two groups there is an increased cancer risk based on family history.

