### Control group

Counselees in the control group will receive standard care only. It is recommended by the Dutch Society for Clinical Genetics that, during the first consultation, counselees are informed about the possible consequences of genetic testing for their relatives [5]. If the genetic counseling result is relevant for relatives, counselees are asked to inform their at-risk relatives. After the last counseling session, counselees receive a summary letter which reaffirms the information provided during the counseling. In case of hereditary cancer, a separate family letter is provided about the test results and recommendations for surveillance measures for the counselees and their relatives. In the Netherlands, although all departments of Genetics consider providing these letters as part of standard care, no specific guidelines are available; this implies that some differences may exist between these letters.

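### The Randomization section announces stratification for three groups but names only two levels, so no stratum is named for counselees in whom DNA testing is not possible

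*Protocol article*

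**What the plan says.** The Participants section describes three kinds of counselee: "those with conclusive test results (a pathogenic mutation has been found"), then "those with an inconclusive test result, and those in whom DNA testing is not possible". It adds of the second and third: "For the latter two groups there is an increased cancer risk based on family history".

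The Randomization section states that "randomization will be stratified for three different groups (that is, conclusive versus inconclusive DNA test result"). After the parenthesis it adds a separate factor, "whether or not the counselee has been diagnosed with cancer". Allocation is 1:1 through ALEA, in random blocks of at most 8, and the stated purpose of stratifying is comparable groups.

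Under Counselees' characteristics, genetic test result and cancer diagnosis are both listed as data to be collected. The Data analysis section describes multilevel models and does not mention the stratification factors. The Ethical and safety issues and Trial status sections say that recruitment is in progress.

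**The concern.** A stratified allocation rule has to assign every eligible person to exactly one cell. Both levels named here are defined by the result of a DNA test. A counselee in whom testing is not possible has no result, so the parenthesis gives that person no level, although the sentence counts three groups and the trial enrols three.

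Two things depend on how this is resolved. The first is whether the arms are balanced on the untested group by design or only by chance. The second is which stratum variable, with how many cells, an analyst could carry into the models. This is not a detail left to a fuller document: the article states the factor and its levels, and the two statements disagree.

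**Working it through.** **Step 1. Count the levels.**

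| Source | DNA-test groups |
|---|---|
| Participants section, groups enrolled | 3 (mutation found; inconclusive; testing not possible) |
| Randomization section, number announced | 3 |
| Randomization section, levels named | 2 (conclusive; inconclusive) |

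**Step 2. Try each reading of the sentence.**

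- *The untested form their own level.* The count of three is right and the parenthesis is incomplete. Strata: 3 x 2 = 6, on average 264/6 = 44 counselees each.
- *The untested are pooled with the inconclusive.* The parenthesis is right and the count of three is wrong. Strata: 2 x 2 = 4, on average 264/4 = 66 each.
- *The cancer-diagnosis factor supplies the third group.* It is a separate factor placed after the parenthesis, and crossing it with two levels gives 4 cells, not three.

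No reading makes the whole sentence true, and nothing elsewhere in the article chooses between 4 and 6.

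**Step 3. Size of the possible imbalance.** The article gives no figure for the untested share, so this step is an illustration. Inputs: 264 counselees (2 x 132, from the abstract and the Sample size section), 1:1 allocation and blocks of at most 8 (Randomization section). Assumed: 53 untested, about 20% of 264.

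If *n* untested counselees are mixed with others in a group of size *N* that is balanced 1:1, the number falling in one arm has mean *n*/2 and approximately

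SD = sqrt(*n* x 0.25 x (1 - *n*/*N*)).

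- Pooled with 100 inconclusive counselees (assumed), *N* = 153: SD = sqrt(53 x 0.25 x (1 - 53/153)) = 2.94. The 95% range is 26.5 +/- 1.96 x 2.94 = 26.5 +/- 5.8, about 21 v 32.
- No stratification on the DNA-test factor at all, *N* = 264: SD = sqrt(53 x 0.25 x (1 - 53/264)) = 3.25. The range is 26.5 +/- 6.4, about 20 v 33. This is wider than the pooled reading allows and serves only as an outer limit.
- Half the assumed share, *n* = 26, pooled with the same 100, *N* = 126: SD = sqrt(26 x 0.25 x (1 - 26/126)) = 2.27. The range is 13 +/- 4.5, about 9 v 17.

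**Step 4. The comparison under six strata.** A 1:1 block of at most 8 that is left incomplete can differ by at most 4 between arms. The untested would occupy two strata (cancer diagnosis yes and no), so the largest possible difference is 4 + 4 = 8. With 53 people, an odd number, that means 23 v 30 at worst. Against 21 v 32 the gain is small; against 9 v 17 (a difference of 8) there is almost none. These compare a 95% range with a worst case, so they somewhat understate the benefit of separate strata.

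**Step 5. Sample size.** The calculation uses effect sizes, a correlation of 0.7, 80% power and a 0.05 level. None of these depends on the number of strata, so 132 per group is unaffected.

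**The case against.** The strongest reply is that the sentence is a loose gloss in a condensed article. The Participants section lists exactly three groups, the Randomization section says three, and the natural inference is that all three are strata. Recruitment is already under way, so ALEA presumably holds definite levels. On that reading balance is secured and only the wording is wrong. This is plausible and it limits the seriousness of the point. It does not remove the contradiction, because pooling would be an equally workable design and the article does not say which was used.

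A reader might infer four stronger things. The documents support none of them.

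- *Untested counselees have no stratum.* The article shows only that none is named for them.
- *The three hospitals code them differently.* Nothing says who enters the stratum or that sites interpret it.
- *The untested must be separated because their relatives' risk rests on family history.* The Participants section says this of the inconclusive group too. Nor does the statement "In case of hereditary cancer, a separate family letter is provided about the test results", in the Control group section, separate the two, since a pathogenic mutation is tied to the conclusive group only. Pooling them would be defensible.
- *The planned analysis would adjust for mixed codes.* The Data analysis section states no adjustment for strata, so harm by that route is conditional.

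**Conclusion.** The point holds as an inconsistency in an operative allocation rule: three groups announced, two named, three enrolled, and a number of strata that could be 4 or 6. The conclusion rests on the text alone and needs no assumption.

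Its consequences are modest. Any imbalance on the untested group would be chance imbalance and not bias, and concealment, sample size and power are untouched. With an assumed 53 untested and 100 inconclusive, pooling allows about 21 v 32, where separate strata would hold the difference to 8 or less. With fewer untested the gain shrinks towards nothing. What remains is that a reader cannot tell whether the third group is balanced by design, and an analyst cannot reconstruct the strata from the article. It should be corrected, at little cost.

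**What to change.** 1. Confirm from the ALEA configuration which levels are in use.
2. Correct the Randomization section to match. If three levels are used, list them as in the Participants section (pathogenic mutation found; tested, inconclusive; DNA testing not possible), crossed with cancer diagnosis yes or no, six strata in all. If ALEA pools the last two, say so, replace the word three, and state that there are four strata.
3. Include the stratification factors, as actually used, as covariates in the models of the Data analysis section. Take the test-result group from the data already collected under Counselees' characteristics, including for counselees already randomized.

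The cost is a check of the system settings, one corrected sentence, and covariates drawn from data already planned. If six strata are used, there are slightly more incomplete blocks: up to six instead of four. In the extreme case where every one falls short in the same direction, the overall arm difference could reach 6 x 4 = 24 instead of 4 x 4 = 16. That outcome is very unlikely.

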### Blinding

The informed consent procedure to postpone information enables a blind design for participants in the control group. Participants in the intervention group will be masked for the exact study objective to avoid biased outcome measures. Psychosocial workers and research assistants who collect data cannot be blinded. At T2, research assistants will obtain outcome measures by telephone. To ensure that the outcomes are obtained as objectively as possible, a telephone script has been developed to minimize individual differences between research assistants. Also, to minimize additional bias, data entry is performed by someone other than the person who performs the analyses.

### Data analysis

All analyses will be based on the intention-to-treat principle. Assuming random dropout, incomplete data will be imputed using data of the control group, that is, standard care.

*Hypothesis 1:* Multilevel analysis will be used to investigate whether the intervention increases counselees’ knowledge, motivation and self-efficacy as compared with the control group. Effects of the intervention will be investigated on each of the seven outcome variables separately. The three moments of measurement (T1, T2, T3) will be treated as nested within counselees.

*Hypothesis 2:* Multilevel analysis will also be used to investigate whether the intervention increases: the number of correctly informed relatives; relatives’ knowledge about hereditary/familial cancer and preventive measures; and relatives’ intention to engage in genetic counseling. For this, the relatives will be treated as nested within counselees and counselees will be treated as nested within physicians.

*Hypothesis 3:* To investigate how counselees and psychosocial workers evaluate the intervention, descriptives and frequencies will be calculated to present counselees’ and psychosocial workers’ evaluation of the intervention.

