## Methods/Design

### Trial design

The study comprises a multicenter RCT with a parallel group design, comparing the effects of an additional telephonic counseling session aimed at supporting counselees in informing their at-risk relatives (intervention group), with a control condition of standard care only. Participating counselees will complete a questionnaire at three moments:

1. Pre-intervention (T1), after receiving a summary letter from the genetic counselor,

2. Post-intervention (T2), immediately following the intervention, or -in standard care - at the same time (about 4 weeks after T1),

3. Follow-up (T3) at 4 months after T1.

At T2 counselees are telephoned to complete items regarding their insight as to who to inform and their knowledge on surveillance measures; the rationale behind the telephone intervention is that these items are too complex to complete alone. At T3, participants will invite at-risk relatives to also complete a questionnaire (Figure 1).

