### Recruitment and informed consent

#### Counselees

In the Netherlands, it is considered standard care for the Clinical Genetics department to send counselees a summary letter after the last counseling session; this letter reaffirms the information provided and aims to facilitate the communication process in the family. When this letter has been received, clinical geneticists and counselors will invite eligible counselees to participate using an information letter, an informed consent form, a return slip to decline participation, and an invitation to complete a (web-based) questionnaire (T1).

We will use a two-stage randomization and a consent procedure with consent to postponed information [34-36]. In this procedure, counselees are masked for the exact study objective. However, they are informed that: 1) the study aims to assess issues pertaining to family disclosure, 2) the study has an additional purpose, and 3) a letter with the postponed information about the additional research question and reasons for not informing them during recruitment will be sent after the study. Postponed information enables a blind design and avoids a less favorable outcome in the control group resulting from their knowledge that the other counselees receive extra care. This procedure has been used previously and resulted in no major objections [35-38].

In case of consent, counselees will be asked to complete a web-based baseline questionnaire (if preferred, a paper version of the questionnaire is available). Counselees will then be randomized (Figure 1). Counselees in the intervention group will receive an information letter about the additional counseling, an informed consent form for the intervention, and a return slip to decline participation. Within one week they will be contacted by telephone to provide them with additional information about the intervention and are asked for their consent. Counselees in the control group will receive no additional information. Information about the randomization procedure will be included in the debriefing letter for counselees, which is sent after the study.

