### Sample size

For the primary research question we aim for a medium effect size. At baseline (T1), we assume no differences in primary outcomes between the intervention and control group. At T2 we expect to find a medium effect size. We assume this to be 0.5 for the intervention group and 0.2 for the control group, taking into account that the outcomes in the control group may be slightly affected by that fact that they are aware that the study focuses on informing their relatives; this effect is estimated to last until follow-up (T3).

Based on these assumptions, we require 132 patients in each group to have 80% power to detect an intervention effect (group/time interaction) that is significant at the 0.05 level (assuming a 0.7 correlation between measurements). In addition, we have a 99% chance to detect differences between measurement moments and a 46% chance to detect group differences overall.

Assuming a response rate of 50% and a 20% dropout, we need to approach 660 counselees. Preliminary work has shown that counselees are advised to inform (on average) 4.6 at-risk relatives. Assuming that counselees provide contact information for (on average) two relatives and that 50% of these relatives will complete the questionnaire, it is estimated that we will have data on 264 relatives.

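### Control-based imputation does not fit the stated assumption of random dropout: at 20% intervention-arm missingness it shrinks the expected T2 effect from 0.30 to 0.24 SD

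*Protocol article*

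**What the plan says.** All statements are in the protocol article.

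- **Data analysis, principle:** "All analyses will be based on the intention-to-treat principle".
- **Data analysis, missing data:** "Assuming random dropout, incomplete data will be imputed using data of the control group, that is, standard care". No other missing-data method is given, and the rule is not described as conservative or as a sensitivity analysis.
- **Data analysis, model for Hypothesis 1:** a multilevel model for each of seven outcome variables, in which "The three moments of measurement (T1, T2, T3) will be treated as nested within counselees".
- **Primary outcome measures:** the primary outcomes are assessed at T2.
- **Sample size, effect:** "At baseline (T1), we assume no differences in primary outcomes between the intervention and control group". For T2, "We assume this to be 0.5 for the intervention group and 0.2 for the control group". The correlation between measurements is 0.7 and the significance level 0.05.
- **Sample size, numbers:** "we require 132 patients in each group to have 80% power to detect an intervention effect (group/time interaction"). A response rate of 50% and dropout of 20% then lead to 660 counselees to be approached. Dropout is not split by arm or time point, and nothing is allowed for a diluted effect.

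**The concern.** The two halves of the rule describe different missing-data models. Under random dropout, an intervention-arm counselee with no T2 value is expected to resemble intervention-arm counselees with the same history who were measured. Taking the value from controls assumes instead that this counselee did no better than under standard care. That is a reference-based assumption, and random dropout does not justify it.

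Only intervention-arm values are affected. Filling control-arm gaps from control data is harmless under random dropout.

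Because the rule sits directly after the intention-to-treat statement and covers all analyses, it reaches every primary outcome. If the plan's own assumption is true, following the plan understates a real effect and loses power.

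**Working it through.** **Inputs from the Sample size section.** Expected effects are 0.5 and 0.2, so the T2 difference is 0.5 − 0.2 = 0.3 SD with none at T1. The correlation is 0.7, alpha 0.05 (two-sided assumed) and dropout 20%.

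**Assumptions added here.** The 20% is missing at T2 in both arms, completely at random. Imputation is by regression on T1 fitted in controls. The T2 comparison is made by change score or by ANCOVA, as simpler stand-ins for the multilevel model.

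**Step 1: the plan's own figure.**
- The change-score SD is √(2 × (1 − 0.7)) = 0.775.
- n per arm = 2 × 0.6 × (1.96 + 0.842)² / 0.3² = 104.7, so 105.
- Allowing for 20% dropout, 105 / 0.8 = 131.25, so 132. The stated 132 is reproduced as a number randomised.
- The article's other arithmetic is 660 × 0.5 = 330 consenting, or 165 per arm, and 330 × 0.8 = 264, or 132 per arm remaining. Both readings are carried forward.

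**Step 2: expected estimate.** Let m be the share of intervention-arm T2 values missing. Observed counselees contribute 0.3 and imputed ones 0, so the expected difference is 0.3 × (1 − m).

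| m | 5% | 10% | 20% | 30% | 40% |
|---|---|---|---|---|---|
| Expected difference (SD) | 0.285 | 0.270 | 0.240 | 0.210 | 0.180 |

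Only the 20% column uses the plan's dropout figure; the others are illustrative. In 4,000 simulated trials with 132 per arm and 20% missing, the mean estimate was 0.240 under the rule and 0.299 from observed data.

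**Step 3: power at 20% missing.** Power ≈ Φ(δ / (SD × √(2/n)) − 1.96). The SD is 0.775 for the change score and √(1 − 0.7²) = 0.714 for ANCOVA. The observed-data analysis uses δ = 0.30 and 0.8n per arm. The stated rule uses δ = 0.24 and n per arm.

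Example, change score, n = 132:
- observed data: 0.30 / (0.775 × √(2/105.6)) = 2.81, power 80%
- stated rule: 0.24 / (0.775 × √(2/132)) = 2.52, power 71% (simulated 70%)

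| Randomised per arm | Analysis at T2 | Observed data | Stated rule |
|---|---|---|---|
| 132 | change score | about 80% | about 70% |
| 132 | ANCOVA | about 85% | about 77% |
| 165 | change score | about 88% | about 79% |
| 165 | ANCOVA | about 92% | about 85% |

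Formula and simulation agree within about one percentage point. If control values were drawn without conditioning on T1, simulated change-score power under the rule would be about 55% (132 per arm) or 64% (165 per arm), with the estimate still at about 0.24.

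**Step 4: limits of the effect.**
- *Type I error.* With no true effect, the rule rejected in 4.7% to 5.6% of simulated trials.
- *Losses at T3 only.* These leave T2 unchanged. If the observed T2 informs the imputation, the expected T3 difference is 0.3 × (0.8 + 0.2 × 0.7/1.7) = 0.265, a smaller shrinkage.

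**The case against.** The strongest defence concerns who goes missing. Counselees in the intervention arm receive, after randomisation, "an informed consent form for the intervention, and a return slip to decline participation". Someone who declines has standard care only, so control data are a sensible guess for that person under intention-to-treat. Suppose the missing 20% are all decliners without benefit and the rest gain 0.30 SD. The true intention-to-treat effect is 0.8 × 0.30 + 0.2 × 0 = 0.24. Control-based imputation then returns 0.24, while the observed-data analysis returns about 0.30 and overstates it.

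This stands, and it rules out a stronger reading. A reader might infer from the second consent that the bias grows with the number who decline the session. The documents do not support that: for decliners without benefit the rule is right. What the defence does not do is rescue the sentence as written, which rests on random dropout and applies to all incomplete data, whatever the reason.

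Other parts of the defence also stand:
- The rule is conservative and does not manufacture false positives.
- The power loss depends on the model, on 132 or 165 randomised per arm, and on how much of the dropout falls at T2. At 165 per arm, power under the rule is still at about the 80% target (change score) or above it (ANCOVA). With 10% missing at T2 and 132 per arm, change-score power is about 81%.
- A reader might also infer that decliners are not followed or have no T2. The article does not say so, and a condensed article may leave such details to the full protocol.

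**Conclusion.** The point holds in a limited form. The stated assumption and the stated imputation rule contradict each other. If dropout is random as assumed, the rule shrinks the expected T2 difference by the factor (1 − intervention-arm missingness): 0.30 to 0.24 SD at 20%. This does not depend on whether 132 or 165 are randomised per arm. The accompanying loss of power is roughly 7 to 10 percentage points under the assumptions shown.

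The harm is an understated effect and reduced power, not a false claim of benefit. The size rests on all of the 20% being missing at T2, which the article does not specify. A heavier loss in the intervention arm, such as 30%, is an illustration and not a prediction. Because the direction is conservative and the rule would suit decliners who are not followed, this is a correction to make before analysis and not a fatal flaw.

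**What to change.** Reconcile the missing-data sentence with the analysis:

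1. **Primary analysis.** Use the multilevel model already planned, fitted by likelihood to all observed T1, T2 and T3 data of all randomised counselees, with no prior imputation. It is valid under the random-dropout assumption that the article states.
2. **Sensitivity analysis.** Keep control-based imputation, done as multiple imputation, and label it conservative. State that it represents counselees who leave the intervention arm without benefit, such as those who decline the session and are not followed. Report both results together so that the reader sees how far the conclusion depends on the assumption.

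The cost is a few sentences in the analysis section and one additional analysis run per outcome. No change to design, recruitment or data collection is needed.

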To address the need to support counselees and the call for an intervention by others [26,27], various interventions have been developed to improve family communication about genetic testing and screening options [28-31]. These interventions mainly comprise enhanced information [29,31] or communication skills training [28,31] for counselees. However, no effects on facilitating the family communication process were found, except for improving counselees’ satisfaction [31]. One study developed a counseling intervention to support counselees in communicating genetic information to at-risk relatives; this intervention comprised the use of a pedigree chart (for example, a document to record medical family history) to explicitly identify at-risk relatives, a follow-up letter stressing the importance of family disclosure, and two follow-up telephone calls during which it was documented which relatives had been informed and offering guidance about how to approach relatives [32]. Investigation of the effectiveness of this intervention indicated that the proportion of at-risk relatives using genetic services was larger in the intervention group (61%) compared with the control group (36%); however, this latter study had a cohort design (instead of a randomized design) thereby limiting the possibility to draw firm conclusions [32].

This paper describes the design of a randomized controlled trial (RCT) for investigating the effectiveness of an intervention based on the principles of Motivational Interviewing (MI) [31]. MI is a client-centered counseling style that helps individuals change health-related behavior, such as sharing hereditary cancer risk information with relatives. We consider that this client-centered but directive counseling style of MI is well suited for counselors, since they have to discuss family communication with counselees while at the same time respecting counselees’ autonomy.

The intervention, consisting of an additional telephone counseling session conducted by psychosocial workers, aims to support counselees in disclosing hereditary or familial cancer risk information to at-risk relatives. This paper presents details of the design of this RCT, guided by the CONSORT checklist [33].

This RCT (registered in the Dutch National Trial Register: NTR3745) aims to test the following hypotheses:

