**Hypothesis 1** - The intervention will increase counselees’ knowledge, motivation and self-efficacy with regard to informing relatives about their hereditary or familial cancer risk, as compared with counselees who receive standard care.

**Hypothesis 2** - The intervention will lead to more at-risk relatives being informed by counselees; increased knowledge among relatives about hereditary/familial cancer and preventive measures; and increased intention of informed relatives to engage in genetic counseling, testing and/or preventive measures, compared with the standard care condition.

**Hypothesis 3** - The intervention will be positively evaluated by counselees and psychosocial workers.

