#### Inclusion criteria

Participants will be counselees who: 1) are the first in their family to visit the Clinical Genetics department for hereditary or familial colon or breast and/or ovarian cancer (referred to as: index patients); 2) have at least one relative at increased risk, that is, eligible for genetic testing and/or surveillance; 3) are aged ≥ 18 years, and 4) are able to read/write Dutch.

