### Primary outcome measures

At T2 the primary outcomes will be assessed by questionnaire (and partly by telephone) using specific instruments (Figure 1). Details on the development and psychometric properties of the outcome measures will be published separately.

Knowledge will comprise counselees’:

1. Insight into which relatives need to be informed, as indicated by a percentage ‘correct knowledge’ specifying the relative number of family members that need to be informed, correctly remembered by the counselee (range 0 to 100).

2. Knowledge about surveillance measures for relatives, as indicated by the percentage ‘correct knowledge about surveillance options’ that indicates how many screening options for relatives (1 to 6), are correctly remembered by the counselee (range 0 to 100).

3. Risk perception, as measured with two items: perceived lifetime breast and/or ovarian or colon cancer risk in percentages, and perceived breast and/or ovarian or colon cancer risk as compared with the average Dutch woman or person (5-point Likert scale: 1 = very strongly lowered, 5 = very strongly heightened).

4. General knowledge about hereditary breast or colon cancer, which includes six items developed by Pieterse *et al*. [42] based on the work of Claes *et al*. [14]. All items are presented as statements with three response categories (‘Correct’, ‘Incorrect’, or ‘I do not know’). A higher score indicates more knowledge about hereditary cancer.

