### Counselees’ characteristics

Counselees’ characteristics include the following:

1. Demographic variables, which include age, gender, educational level, age of their children, and marital status.

2. Clinical characteristics, comprising genetic test result, cancer diagnosis, number of relatives to be informed, number of informed relatives (as reported by the counselee), age at which the counselee was first confronted with cancer in the family, and types of cancer in the family.

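### Hypothesis 2 words disclosure as a count with no denominator but models it per relative; analysed as a raw count, it can lose considerable power

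*Protocol article*

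**What the plan says.** All references are to the protocol article.

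- **Background, Hypothesis 2:** "The intervention will lead to more at-risk relatives being informed by counselees". No share is mentioned.
- **Data analysis, Hypothesis 2:** multilevel analysis is planned "to investigate whether the intervention increases: the number of correctly informed relatives", together with relatives' knowledge and intention. One structure is given for all three outcomes: "the relatives will be treated as nested within counselees and counselees will be treated as nested within physicians". No denominator, offset or adjustment is named.
- **Secondary outcome measures:** disclosure by the counselee is not listed, so the Data analysis section holds its only working definition.
- **Counselees' characteristics:** two totals per counselee are recorded, "number of relatives to be informed, number of informed relatives (as reported by the counselee". Both are classed as clinical characteristics.
- **Inclusion criteria:** a counselee must "have at least one relative at increased risk".
- **Sample size:** "counselees are advised to inform (on average) 4.6 at-risk relatives". No SD is given, and no power is stated for Hypothesis 2.
- **Primary outcome measures:** the parallel knowledge item does use a denominator, "specifying the relative number of family members that need to be informed, correctly remembered by the counselee (range 0 to 100".

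**The concern.** A number of informed relatives is a property of the counselee: one value each. A model with relatives at its lowest level needs one value per relative. The outcome as worded and the model as stated therefore cannot both apply, and the two ways out give different estimands.

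If the wording is followed and the raw count is compared between arms, the result is capped by family size. A counselee who informs 1 of 1 relative has disclosed fully and scores 1; one who informs 4 of 12 scores 4. The session is meant to change how completely counselees inform their at-risk relatives (Table 1 lets it end early once all of them have been properly informed). It does not target how many at-risk relatives there are. Spread in family size then becomes noise around the trial's main behavioural outcome, and a real rise in the share informed could be missed.

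**Working it through.** **The article's own figures.** The only power statement concerns the primary question. With group differences of 0, 0.3 and 0.3 at T1, T2 and T3, SD 1, first-order autoregressive correlation 0.7 and a Geisser-Greenhouse adjusted F test (the last two are assumed readings), 132 per arm gives 80.2% for the interaction and 46.2% for the overall group effect. The stated 80% and 46% reproduce, as does 264/(0.5 × 0.8) = 660. Nothing below touches them.

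**Inputs.** From the article: 132 per arm, and number of at-risk relatives *m* ≥ 1 with mean 4.6. Assumed because the article does not give them: SD of *m*, share informed *p*, within-counselee correlation ρ, and two-sided 0.05. Middle case: SD 3, 60% versus 72%, ρ = 0.3.

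**Raw count.** Var(Y) = p(1−p)[E(m) + ρE{m(m−1)}] + p²Var(m).

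- E{m(m−1)} = 9 + 4.6² − 4.6 = 25.56; the bracket is 4.6 + 0.3 × 25.56 = 12.27.
- Control: 0.24 × 12.27 + 0.36 × 9 = 2.94 + 3.24 = 6.18. Family size is 3.24/6.18 = 52% of the variance.
- Intervention: 0.2016 × 12.27 + 0.5184 × 9 = 2.47 + 4.67 = 7.14. Family size is 65%.
- Difference: 0.12 × 4.6 = 0.552 relatives. SE = √[(6.18 + 7.14)/132] = 0.318.
- Power = Φ(0.552/0.318 − 1.96) = Φ(−0.22) = 41%.

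**Pooled share** (all informed over all at-risk, variance clustered by counselee). The p²Var(m) term drops out: SE = √[(2.94 + 2.47)/132]/4.6 = 0.0440. Power = Φ(0.12/0.0440 − 1.96) = Φ(0.77) = 78%.

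**Mean of the per-counselee shares.** Variance p(1−p)[ρ + (1−ρ)E(1/m)]. With *m* as 1 plus a negative binomial, E(1/m) = 0.344, SE = 0.0425 and power 81%.

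Simulation of the middle case agrees: about 42% for the raw count, 79% for the mean share, and 76–77% for the count adjusted for the number to be informed.

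**Over a range** (same formulas, 132 per arm):

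| Informed | SD of m | ρ | Raw count | Pooled share | Mean share |
|---|---|---|---|---|---|
| 60% v 72% | 2 | 0.1 | 70% | 96% | 94% |
| 60% v 72% | 3 | 0.3 | 41% | 78% | 81% |
| 60% v 72% | 4 | 0.5 | 26% | 55% | 69% |
| 60% v 70% | 1 | 0.1 | 78% | 88% | 87% |
| 36% v 61% | 3 | 0.3 | 98% | >99% | >99% |
| 36% v 61% | 4 | 0.5 | 88% | 99% | >99% |

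The pair 36% and 61% is the only set of two-group proportions in the article. It comes from the Background, for uptake of genetic services in an earlier non-randomised cohort study. It is not a disclosure rate.

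**False positives.** With 60% informed in both arms in the middle case, the t-test on raw counts rejected in about 5% of simulated trials.

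**The case against.** **The nesting may already mean a per-relative analysis.** Read that way, each at-risk relative is scored informed or not, "number" is loose prose, and the denominator is built in. This stands as a possible reading, so the raw count cannot be taken as settled. It does not remove the point: the text supports two estimands with different power, and the choice should be fixed before the data are seen.

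**A covariate would recover most of the loss.** This also stands in the middle case (76–77% against 79% for the share), and a full analysis plan may name covariates. But covariates do not cure the mismatch between a one-per-counselee outcome and a relative-level model.

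**A count answers Hypothesis 2 as worded.** True. A count is not invalid; it measures something different from completeness of disclosure.

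Three stronger readings are tempting, and the document does not support them:

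- *Family size swamps the effect and much of the power is lost.* This depends on the spread of family size, the share informed and the correlation, none of which is given. With SD 1, or with 36% versus 61%, the loss is modest.
- *A larger average family in one arm can pass for an effect.* Randomisation balances family size in expectation. In the middle case the SD of the chance difference in mean family size is √(2 × 9/132) = 0.37, worth 0.6 × 0.37 = 0.22 relatives, but that variation is already in the standard error of 0.318, and the error rate stays near 5%.
- *Family size differs by test result.* The article does not say so, and randomisation is stratified by test result.

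**Conclusion.** The mismatch between outcome and model is on the page and needs no assumption: a count per counselee, without a denominator, is assigned to a model whose lowest level is the relative. The consequence is conditional. If the raw count is analysed, power can fall considerably, to about 42% against about 79% for the share in the middle case; the gap widens with the spread of family size and shrinks as the effect grows. These figures rest on an assumed SD, shares and correlation. The harm is lost precision and an outcome that is hard to read across families of different size, not bias or excess false positives. It concerns a secondary hypothesis and leaves the 132 per arm for the primary question as it is. The wording should be corrected because the remedy is cheap.

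**What to change.** In the Data analysis section, define the disclosure outcome as informed yes/no for each at-risk relative on the pedigree as it stood at randomisation. Analyse it with a logistic mixed model, relatives within counselees within physicians, which is the nesting already stated. The rows should be all at-risk relatives on the pedigree, not only those who return a questionnaire.

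If only totals per counselee are available, model the number informed out of the number of relatives to be informed with a binomial model that allows for overdispersion. At the least, adjust the count for the number to be informed. Report the absolute number informed per arm descriptively.

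The cost is wording. Both totals are already recorded; the per-relative version needs the informed status kept by relative. The small downside is that the effect is read per relative, as an odds ratio or a difference in shares, and not as extra relatives informed per family.
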